**Objective:**

The primary effectiveness objective is to compare the effectiveness of the Essential Coaching for Every Mother program on maternal psychosocial outcomes (self-efficacy, social support, postpartum depression, and postpartum anxiety) immediately after the intervention and 6 months postpartum, collectively as well as stratified by parity. The primary implementation objective is to evaluate the implementation extent and quality of the Essential Coaching for Every Mother program.

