### Effectiveness Objectives

The primary effectiveness objective of this study is to compare the effectiveness of the Essential Coaching for Every Mother program to standard care on self-efficacy measured immediately after the intervention. The secondary objectives are (1) to compare the effectiveness of the Essential Coaching for Every Mother program to standard care on social support, postpartum anxiety, and postpartum depression immediately after the intervention; (2) to determine whether the effect on any outcomes differs based on parity (multiparous or primiparous); and (3) to compare any long-term impacts of the Essential Coaching for Every Mother program on the above outcomes at 6 months postpartum.

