### Effectiveness Hypotheses

The primary hypothesis is that the Essential Coaching for Every Mother program will result in higher self-efficacy for participants who receive the intervention compared with standard care. The secondary hypotheses are that (1) Essential Coaching for Every Mother will result in higher levels of social support, lower levels of postpartum anxiety, and lower levels of postpartum depression for those who receive the intervention compared with standard care; (2) there will be no difference based on parity on any of the psychosocial outcomes; and (3) changes in psychosocial outcomes will be maintained over time.

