### Effectiveness Outcomes

The primary outcome of self-efficacy will be measured using the Karitane Parenting Confidence Scale (KPCS) [32]. This 15-item scale assesses the perceived self-efficacy of mothers of infants up to 12 months of age and has acceptable internal consistency (Cronbach α=.81) and test-retest reliability (*r*=0.88) [32]. A cutoff score of ≤39 (out of a possible 45) was determined to indicate a clinically low level of perceived parenting self-efficacy [32]. Additionally, a reliable change index of ≥6 was considered a significant change in their level of parental self-efficacy. Therefore, parents can be considered to have a high level of parenting self-efficacy if they either have a score above 39 or improve their score by 6 points, while still less than 39 [32]. This measurement will be collected at baseline and 6 weeks and 6 months postpartum.

Social support will be measured using the Multidimensional Scale of Perceived Social Support (MSPSS) [33]. This scale provides a measurement of how much support a parent feels they receive from family, friends, and a significant other, and 3 subscale scores (with 4 items per subscale) can be calculated as well as a total score (from 12 to 84), with total scores indicating greater perceived support. If the total score and subscale scores are averaged over items, scores between 1 and 2.9 are considered “low support,” 3 to 4.9 are considered “moderate support,” and 5 to 7 are considered “high support” [34]. The MSPSS has been shown to be valid and internally reliable, with Cronbach α values ranging from .81 to .94 on individual subscales and from .83 to .92 for the total score [33].

Postpartum anxiety will be measured using the Postpartum Specific Anxiety Scale (PSAS) [35]. The PSAS is a valid and reliable instrument for assessing anxiety during the first 6 months postpartum, with Cronbach α values for individual factors ranging from .80 to .91, with an overall α value of .95 [35]. The optimal cutoff PSAS score for detecting clinical levels of anxiety is 112, with a sensitivity and specificity of 0.75 [35].

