### Data Analysis

Data will be analyzed on an intention-to-treat basis (excluding women who requested to stop receiving the messages or were lost to follow-up). Demographic characteristics on maternal age, marital status, education level, and delivery method will be expressed as means and standard deviations or percentages, as applicable, based on group allocation. Postnatal contacts for themselves and their infants, health concerns, and feeding behavior will also be expressed as means and standard deviations or percentages, as applicable, based on group allocation. Any significant differences in baseline characteristics, examined through a chi-square analysis or Mann-Whitney test, will be adjusted for in the analysis. A *P* value of 0.05 will be considered significant for all outcomes.

For the primary outcome of self-efficacy, a total score will be reported using means, standard deviations, and percentages. Analysis of covariance (ANCOVA) will be used to measure whether total self-efficacy scores differ between the 2 groups, with adjustments for the pretest scores and any significant baseline characteristics.

For the first secondary objective, an ANCOVA will be used to determine whether scores differ between the 2 groups on social support, postpartum anxiety, and postpartum depression, with adjustments for the pretest scores and any significant baseline characteristics. For the second secondary objective, a 2-way ANCOVA will be used to measure whether the mean difference of self-efficacy scores differs between the 4 groups (multiparous/primiparous and intervention/control), with adjustments for any significant covariates on self-efficacy, social support, postpartum anxiety, and postpartum depression. For the third secondary objective, a 2-way repeated-measures ANCOVA will be used to explore whether changes in the key psychosocial outcome variables varied over time.

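### The analysis assigned to the 6-month objective asks whether outcomes changed over time and names no between-arm difference at 6 months

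*Protocol article*

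**What the plan says.** Effectiveness Objectives gives the third secondary objective as "to compare any long-term impacts of the Essential Coaching for Every Mother program on the above outcomes at 6 months postpartum". The sentence does not repeat the comparator, but the primary and first secondary objectives set it as standard care. The abstract's objective also places the comparison of effectiveness at both times: "immediately after the intervention and 6 months postpartum, collectively as well as stratified by parity".

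Effectiveness Hypotheses words the matching hypothesis differently, as "changes in psychosocial outcomes will be maintained over time".

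In Data Analysis, the method for this objective is that "a 2-way repeated-measures ANCOVA will be used to explore whether changes in the key psychosocial outcome variables varied over time". The sentence names neither the arms, nor the time levels, nor a contrast at 6 months. The same section is explicit elsewhere. Its method for the first of the secondary objectives reads "an ANCOVA will be used to determine whether scores differ between the 2 groups on social support, postpartum anxiety, and postpartum depression"; the pretest score is a covariate there. The primary analysis is worded in the same between-group way.

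On data collection, Effectiveness Outcomes says of the self-efficacy scale: "This measurement will be collected at baseline and 6 weeks and 6 months postpartum". Table 1 shows the other three psychosocial outcomes at the same three times.

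**The concern.** The objective asks how the two arms compare at 6 months. The assigned analysis asks whether changes varied over time. These are different questions, and their answers can point in opposite directions.

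All of the trial's evidence on lasting benefit comes from this one analysis. If the text stands, a significant time effect, which could arise in both arms without any program effect, could be reported as long-term impact. Equally, a non-significant interaction could be reported as no long-term impact when the benefit had in fact been fully kept.

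**Working it through.** **Step 1: what each term of the model tests.** Take the reading most favorable to the plan: arm and time are the two factors, baseline is a covariate, and the time levels are 6 weeks and 6 months. Let d6w and d6m be the true arm differences at the two visits.

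- Time effect: change from 6 weeks to 6 months, pooled over arms. It is not a randomised comparison.
- Arm main effect: (d6w + d6m)/2.
- Arm-by-time interaction: d6w − d6m.
- Quantity the objective needs: d6m.

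None of the first three equals d6m. If baseline is instead a third time level, the overall interaction can be significant whether a 6-week benefit lasted or disappeared, so it does not isolate 6 months either.

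**Step 2: inputs for an illustration.** The plan gives no figure for the 6-month analysis, so there is none to reproduce. Its sample size section supplies a scale: a difference of 3.78 with SD 4.5. Used as a two-group comparison at two-sided alpha 0.05 and an assumed 90% power, n = 2 × (1.960 + 1.282)² × (4.5/3.78)² = 29.8, or 30. That matches the stated 30 per cluster, and 60 × 1.15 = 69 matches the stated inflation. The plan does not state its power, and the role of its intraclass correlation of 0.2 could not be reproduced. Nothing below depends on either.

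Other inputs:
- Analysed per arm: 140 × (1 − 0.155) = 118.3, about 59 per arm. This uses the feasibility study's incompletion rate and assumes no further loss by 6 months.
- Correlation ρ between any two visits: 0.3 to 0.7 (assumed).
- Alpha: "value of 0.05 will be considered significant for all outcomes"; two-sided is assumed.

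**Step 3: standard errors**, each multiplied by √(2/59) = 0.184:
- 6-month difference, baseline-adjusted: 4.5 × √(1 − ρ²)
- Interaction: 4.5 × √(2(1 − ρ))
- Arm effect averaged over visits, baseline-adjusted: 4.5 × √((1 + ρ)/2 − ρ²)

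Example at ρ = 0.5: the standard errors are 0.717, 0.829 and 0.586. For a benefit of 3.78 that falls to 0, the interaction has z = 3.78/0.829 = 4.56 (power 0.995). The averaged arm effect has z = 1.89/0.586 = 3.23 (power 0.897). The true 6-month difference is zero.

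**Step 4: probability of a significant result, ρ from 0.3 to 0.7.**

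| True effect at 6 weeks, 6 months | Arm difference at 6 months | Arm-by-time | Arm effect averaged |
|---|---|---|---|
| 3.78, 3.78 | 0.998 to 1.000 | 0.05 | 1.000 |
| 1.89, 1.89 | 0.667 to 0.891 | 0.05 | 0.862 to 0.967 |
| 3.78, 1.89 | 0.667 to 0.891 | 0.487 to 0.838 | 0.996 to 1.000 |
| 3.78, 0 | 0.05 | 0.971 to 1.000 | 0.862 to 0.967 |

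The first and last rows carry the point. A fully kept benefit leaves the interaction at its false-positive rate. A benefit that has gone makes both the interaction and the averaged arm effect significant most of the time.

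**The case against.** **Arm is probably in the model.** A reader might infer that the plan estimates no treatment effect at 6 months. The text does not support that. The sentence just before uses the term 2-way for two crossed factors, one of them intervention versus control, so arm by time is the natural reading here. From such a model the 6-month difference can be derived by combining the arm and interaction terms. What stands is narrower: the contrast that answers the objective is not named, and the stated question points to a different one.

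**The analysis fits the hypothesis.** Whether effects are maintained is a question about change, and the interaction addresses it. This is correct. It shows that the objective and the hypothesis ask different things. Maintenance also says little on its own: two arms that never differed would show a null interaction too.

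**Complete cases.** A reader might infer that the plan keeps only women who answered every survey. No sentence says so. It would follow only if the repeated-measures ANCOVA were fitted in its classical form, and estimation details may sit in a fuller document. The stated exclusion, "excluding women who requested to stop receiving the messages or were lost to follow-up", is in the text, but it is a matter of the analysis population that a change of model would not by itself remove. The size of any loss cannot be given either, because the document has no 6-month attrition figure. A woman who answers at 6 weeks but not at 6 months would inform the 6-month estimate only indirectly, through the correlation between visits.

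**Preference.** With two follow-up visits and complete data, the two models give essentially the same arm-by-visit test, and the plan describes this analysis as exploratory. That is fair. The main gain comes from naming the estimate.

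**Conclusion.** The point holds as a mismatch between a stated objective and the stated question of its analysis. It should be corrected, but it concerns what the body of the article calls a secondary objective and leaves the 6-week primary analysis untouched.

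The logic needs no numerical assumption: the 6-month arm difference is not the time effect, the averaged arm effect or the interaction. The probabilities are illustrative. They borrow a pre-post change from the feasibility study as if it were a between-arm effect, use its SD for both visits, assume equal correlation between visits and no loss after 6 weeks, and apply to self-efficacy only. The document gives no comparable figures for the other three outcomes.

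The missing-data point is secondary and conditional. If the classical form is used, women missing either follow-up are dropped, including someone who skipped 6 weeks and answered at 6 months. Such a pattern is possible, since Follow-Up Assessments sends both surveys to all participants. How many women this would affect is not known.

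**What to change.** State that the estimate for the third secondary objective is the baseline-adjusted difference between arms at 6 months, with a 95% CI, for each of self-efficacy, social support, postpartum anxiety and postpartum depression.

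Take it from a mixed model with the 6-week and 6-month scores as outcomes and with arm, visit, arm-by-visit, baseline score and parity as fixed effects. Report the arm-by-visit contrast separately, as the answer to the maintenance hypothesis, and read it beside the 6-month difference. Align the wording of the objective and the hypothesis so that each points to its own estimate.

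Say that the model includes every woman with a baseline score and at least one follow-up score, and reconcile this with the exclusion of women lost to follow-up in the same section; otherwise that exclusion could still remove women whom the model would keep.

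The cost is slightly more programming and a few sentences of text. It needs no new data, visits or participants.

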## Results

Study recruitment started on January 5, 2021, and is currently ongoing, with an anticipated date of recruitment completion of January 2022.

## Discussion

Given the lack of standardized postpartum education and support currently available, Essential Coaching for Every Mother is proposed to be an innovative solution to bridge this gap without adding a significant burden to the health care system. The goal of mHealth interventions in postnatal education is not to replace the need for in-person follow-up contacts, as these are important for health assessments of the woman and her infant by a skilled health care provider. Instead, mHealth interventions can be used to complement existing postnatal care by providing timely, standardized, relevant, and evidence-based information directly to women.

It is important to use a hybrid effectiveness-implementation design to evaluate both the Essential Coaching for Every Mother program and the process evaluation implementation to be able to offer suggestions for real-world implementation. This is the first postpartum text message program designed for women in Canada. It is expected that the findings will offer insights into whether the use of mobile technologies could be an effective strategy to ensure that research findings are effectively communicated to mothers to enhance postnatal experiences and care delivery in Nova Scotia. This strategy will also help to support the longevity of the research and may be easily transferable to other health centers and hospitals in Canada.

## Appendix

Multimedia Appendix 1 Peer-review report.

## Abbreviations

ANCOVA: analysis of covariance
CONSORT-EHEALTH: Consolidated Standards of Reporting Trials of Electronic and Mobile HEalth Applications and onLine TeleHealth
EPDS: Edinburgh Postnatal Depression Scale
KPCS: Karitane Parenting Confidence Scale
mHealth: mobile health
MSPSS: Multidimensional Scale of Perceived Social Support
PSAS: Postpartum Specific Anxiety Scale
REDCap: Research Electronic Data Capture
TIDieR: Template for Intervention Description and Replication
